## Abstract

**Background:**

Healthy aging is associated with a decline in multiple functional domains including perception, attention, short and long-term memory, reasoning, decision-making, as well as cognitive and motor control functions; all of which are significantly modulated by an individual’s level of alertness. The control of alertness also significantly declines with age and contributes to increased lapses of attention in everyday life, ranging from minor memory slips to a lack of vigilance and increased risk of falls or motor-vehicle accidents. Several experimental behavioral therapies designed to remediate age-related cognitive decline have been developed, but differ widely in content, method and dose. Preliminary studies demonstrate that Tonic and Phasic Alertness Training (TAPAT) can improve executive functions in older adults and may be a useful adjunct treatment to enhance benefits gained in other clinically validated treatments. The purpose of the current trial (referred to as the Attention training for Learning Enhancement and Resilience Trial or ALERT) is to compare TAPAT to an active control training condition, include a larger sample of patients, and assess both cognitive and functional outcomes.

**Methods/design:**

We will employ a multi-site, longitudinal, blinded randomized controlled trial (RCT) design with a target sample of 120 patients with age-related cognitive decline. Patients will be asked to complete 36 training sessions remotely (30 min/day, 5 days a week, over 3 months) of either the experimental TAPAT training program or an active control computer games condition. Patients will be assessed on a battery of cognitive and functional outcomes at four time points, including: a) immediately before training, b) halfway through training, c) within forty-eight hours post completion of total training, and d) after a three-month no-contact period post completion of total training, to assess the longevity of potential training effects.

**Discussion:**

The strengths of this protocol are that it tests an innovative, in-home administered treatment that targets a fundamental deficit in adults with age-related cognitive decline; employs highly sensitive computer-based assessments of cognition as well as functional abilities, and incorporates a large sample size in an RCT design.

**Trial registration:**

ClinicalTrials.gov identifier: NCT02416401.

## Background

Healthy aging is associated with a decline in multiple functional domains including perception, attention, short and long-term memory, reasoning, decision-making, as well as cognitive and motor control functions [1–3]. Studies show that cognitive decline is paralleled by the atrophy of the neuromodulatory control machinery that crucially supports synaptic plasticity, and its deterioration is a primary contributor to widespread structural and functional brain changes (e.g., reduction in cortical thickness, alterations in myelination, reduction in blood flow/perfusion, reduced resting state connectivity [4]).

Research in age-related cognitive decline has identified four inter-related classes of deficits that can all be expected to be altered as a consequence of neuromodulatory system atrophy: 1) processing speed loss, marked by the slowing of information processing at every neurological level [5]; 2) loss of inhibitory control, which contributes to impairments in background (noise and distractor) suppression [6–8], 3) degraded perceptual processing [9, 10], which necessarily limits all aspects of higher-order cognitive processing; and 4) deterioration of explicit cognitive and movement control processes [6]. Natural or plasticity-based changes in processing speed arise as a product of perceptual degradation and an increase in neural process noise.

Considered from another perspective, processing speed, distractor suppression and perceptual acuity are all significantly modulated by an individual’s level of cognitive alertness [11]—the control of which also significantly declines with age. Decline in alertness, a function important for sustained attention contributes to increased lapses of attention in everyday life, ranging from minor memory slips to a lack of vigilance and increased risk of falls or motor-vehicle accidents. In fact, a recent study has compellingly shown that sustained attention performance can provide an objective cognitive marker for frailty progression in older adults [12]. Alertness and sustained attention rely on a broad network of regions that include the locus coeruleus (LC) in the brainstem, the right inferior frontoparietal regions, medial prefrontal cortex, and the DMN [13, 14]. The LC synthesizes norepinephrine (NE), an excitatory neurotransmitter intimately involved in arousal, and innervates the entire cerebral cortex as well as subcortical regions. Predominantly right inferior frontoparietal, amygdala, and medial prefrontal regions send feedback projections to the LC, regulating its output. Considering the complexity of this system, age-related decline in alertness and sustained attention may be caused by both reduction in NE neurons in the LC, and/or impaired interactions between the LC and associated cortical regions [15, 16].

Sustained attention, particularly as it relates to the examination of novel stimuli, also depends on the integrity of another key neuromodulator, the nucleus basalis (NB) in the basal forebrain [17, 18]. NB activity is associated with the release of acetylcholine (Ach), and has been shown to play an important role in both the attention-based modulation of cortical activity [18] and the suppression of background noise and distractors [19]. The NB or forebrain/cholinergic/system also suffers age related declines in efficiency as a prelude to neurodegenerative disease and has been shown to be a critical enabler of experience-dependent plasticity [20].

Many additional factors contribute to cognitive decline in healthy aging [21, 22], and prior training studies have targeted – and driven improvements in – age-related deficits (e.g., perceptual processing, speed of processing, working memory and executive function) [23]. However, failure to address the deterioration of processes related to the regulation of alertness and sustained attention (e.g., the modulation of forebrain activities controlled by selective or phasic attention; suppression of background distractors; engagement of attention and reward-system responses that directly regulate synaptic change) can be expected to attenuate or frustrate efforts to improve age-related cognitive decline, and leave the path open for continuing decline [24].

Several experimental behavioral therapies designed to remediate age-related cognitive decline have been developed over the last 10–12 years. However, methodological weaknesses, such as small sample sizes, lack of adequate controls, and limited outcome measures have made it difficult to interpret the meanings of both significant and nonsignificant findings [25–27]. To date, experimental interventions for age-related cognitive decline have differed widely in content, method and dose, and there is an ongoing debate regarding the question of whether training can improve untrained cognitive abilities (i.e., effects that generalize across cognitive domains). Not surprisingly, no treatment has been widely adopted and there is no consensus about which therapy is most effective [28].

Thus, to address current knowledge gaps and target age-related cognitive deficits, we have developed a treatment targeting both sustained (tonic) and moment-to-moment (phasic) aspects of attention (tonic and phasic alertness training, TAPAT). TAPAT is a continuous performance task in which all stimuli are presented at central fixation with several key elements that help older adults to stay engaged such as jittered inter-trial intervals [29, 30], rich, colorful, and novel stimuli, and a response inhibition component. In a preliminary trial of TAPAT [31], healthy older adults were randomly assigned to treatment or an active control group (AC); participants in the treatment group engaged in the computerized, continuous performance training task that required that they remain alert and engaged (tonic alertness), responding quickly to all non-target objects, scenes or sounds while waiting for an unpredictable and infrequent target object or scene [32–34]. Critically, participants were challenged to inhibit the prepotent motor response (phasic alertness) when they saw the target stimulus. Following ~ 5 h of training over six weeks, participants demonstrated improvements in inhibitory control (withholding response) and sustained attention (reduction in response time variability) in the training task. Also, participants in the TAPAT training group showed significant improvement in speeded visual selective attention compared to participants in the AC group. Moreover, the results show that training related improvement in sustained attention and inhibitory control generalize to untrained, challenging measures of executive function (e.g., working memory, fluency, set-shifting). Magnitude of improvement in the training task (target accuracy) was significantly correlated with the magnitude of improvement in executive function. Finally, when participants were trained in a secondary perceptual learning task, learning rates were accelerated and the level of improvement achieved were greater when that training was preceded by a short epoch of TAPAT training, compared to the AC. The results are consistent with recent, parallel studies in which participants with acquired brain injury also showed improvements in spatial and non-spatial attention, and executive functions [35], following TAPAT training versus participants in wait-list or active control training conditions [32–34].

### Aims and hypotheses

The aim of the current study is to test the effectiveness of a longer (12–16 weeks) version of computer-based TAPAT training to improve cognitive abilities (e.g., attention, working memory, executive function), functional status and quality of life of individuals with age-related cognitive decline as compared to a computer-based active control. Secondary aims include measuring the degree to which these effects persist after a three-month no-contact period, and also demonstrate equivalency in safety reported between the treatment and control groups (FDA requirement).

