## Methods

### Overall design and timeline

The current study will employ a multi-site, longitudinal, blinded randomized controlled trial (RCT) design with a target sample of 120 older adults without dementia or MCI (see inclusion criteria below). Sixty older adults completing TAPAT will be compared to sixty older adults completing the active control condition (computer-based games; see Fig. 1). Total participation time is approximately 6 months and includes 5 in-person assessment sessions. Assessments will be performed at University of Iowa (Iowa City, IA) and VA Boston Healthcare System (Boston, MA). The first assessment session (V0) involves screening for eligibility (see inclusion/exclusion below). If the participant is eligible, baseline assessments are administered in a second visit (V1) to characterize their cognitive and functional abilities before training. After the baseline assessment, older adults are randomized to either the TAPAT or control training program and complete approximately 12–16 weeks of in-home training, while monitored and coached by a research assistant (*cognitive remediation coach*). Participants assigned to the experimental software treatment program will be randomly assigned to receive performance feedback (version A.1 vs. A.2) in the first or the second half of training. Participants will then be asked to complete a mid-training assessment (V1.5) and will be administered a subset of assessments comprised of the secondary outcome: mindfulness. At the mid-training assessment, participants who were randomized to the experimental program will switch program versions (i.e., participants that trained on version A.1 will begin version A.2, and vice versa), such that participants train on both versions. To measure potential training-related improvements, participants will be assessed immediately after the completion of the total training (V2) by an assessor that is blind to group affiliation. To measure the persistence of potential training-related improvements, participants are also assessed after a three-month no-contact period (V3), again by an assessor blind to group affiliation. After this visit, participant activities are completed and trial participation ends.

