### Randomization

Participants will be randomized after the baseline visit and before the planned first day of program use. All V0 and V1 data for each participant must be fully monitored, with all queries resolved, before randomization may take place. We will use a randomization server (sealedenvelope.com) that implements the random permuted blocks within strata procedure [49, 50] with strata as age (*Older Adults 65–74* or *Older Adults* ≥ 75 years of age), allocation ratio is 1:1. Participants who are randomized to the experimental treatment group will also be randomized to either receive version 1 (experimental treatment with performance feedback) or version 2 (experimental treatment without performance feedback); at the mid-training assessment, participants will undergo a reversal of the version type such that all participants completing the entirety of the training will have trained on both versions of the experimental training program. The Site Coordinating Center will issue a randomization assignment at the appropriate time. This approach represents a best practice approach to randomization, implementing an automated centralized group assignment procedure with allocation concealment, and effective separation of sequence generation and allocation concealment.

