We will conservatively follow guidelines for medical devices in the reporting of adverse events in this trial, which defines unanticipated adverse device effects (UADEs) in The Code of Federal Regulations in 21 CFR 812.3(s) as any serious adverse effect on health or safety of any life-threatening problem or death caused by, or associated with, a device, if that effect, problem, or death, was not previously defined in nature, severity or degree of incidence in the investigational plan or application (or supplementary plan or application). Furthermore, an effect is classified as an UADE if it is judged by the Site PI to be a serious problem associated with a device that related to the rights, safety, or welfare of participants. We will operationalize this definition of a serious problem as one that results in any of the following outcomes: death, life-threatening situation, inpatient hospitalization atypical of the participant’s diseases condition, persistent or significant disability/incapacity; or any other adverse event that, based upon appropriate medical judgment, may jeopardize the participant’s health or the health and well-being of all participants enrolled in the study.

Site Study Coordinators, Psychometricians, and Cognitive Remediation Coaches will ask about any UADEs during each contact with participants and will be alert to any volunteered UADEs. All UADEs will be documented on a standardized eCRF and will be classified by the blinded Site PI to their degree of seriousness and their relationship to the study software.

All UADEs, whether or not we believe them to be related to the protocol, will be reported to the Site IRB according to the investigational site’s IRB procedures and to Study PI ([name]) as soon as possible, but in all cases within 10 working days of the event. PSC will circulate UADE reports to the Research Monitor and all trial sites within 10 working days of receipt. Each study site will report immediately to: 1) University of Iowa IRB, 2) PSC IRB, or 3) At the Boston VA, UADEs will be reported to the VA Central IRB electronically through a secure SharePoint system and confirmed by phone to [name].

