### The secondary outcome measures are:

Gradual onset Continuous Performance Task (target accuracy, raw score)Stop Signal task (time interval for successful stop, raw score)
Flanker task (reaction time in incongruent flanker trials – congruent flanker trials, raw scores)Cross-modal Stroop – Mixed Signals (reaction time in response conflict trials, raw score)WAIS IV Digit Span, forwards and sequencing (raw scores)Spatial Working Memory task (accuracy, raw score)DKEFS Verbal Fluency, phonemic and semantic subtest (raw scores)Reinforcement Learning task (bias index)WMS IV Logical Memory I & II immediate recall (sum of learning trials, raw score)WMS IV Logical Memory I & II delayed recall (sum of recall trials, raw score)Walking Behavior Measure (raw score)Self-efficacy Assessment (two scales, raw scores)Falls Efficacy scale (raw score)Timed Up and Go task –TUG (time to completion, raw score)SF-12 (raw score)Cognitive Failures Questionnaire (raw score)Pittsburg Sleep Quality Index (raw score)Mindful Attention Awareness Scale – MAAS (raw score)Breath Counting task (accuracy, raw score)

The primary analysis time point is V2, the post-training assessment. The secondary analysis time point is V3, the follow-up assessment.

The primary statistical analysis methodology is a linear mixed model approach. We will first compare treatment and active control groups in the ITT population to determine if any differences in baseline demographic, characterization, outcomes variables, or total program use time remain after the randomization process. Any such factors that show trend level significant differences (*p* < 0.1) will be noted and used as covariates in the linear mixed model analysis. We will examine the data from each outcome measure using a linear mixed model with group and time as fixed factors, site as a random factor, and co-variates as necessary from the baseline analysis. Missing data will be handled with an iterative maximum likelihood procedure to optimally estimate model parameters. The key value for significance will be the group by time interaction factor for the model.

The criterion for statistical significance is *p* < 0.05. Results with *p* < 0.1 will be described as trends.

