The current study is designed to the highest standard of RCT (e.g., blinded and deals with appropriate allocation concealment). Moreover, this protocol will measure immediate as well as lasting benefits of treatment. Lastly, many previous studies lacked statistical power due to a small sample size. ALERT is appropriately powered to detect improvements in targeted cognitive operations. We have statistically powered the study to detect a between groups Cohen’s d effect size of 0.50 on an outcome measure, calculated as the between group difference in the treatment effect means (post-assessment score minus pre-assessment score) divided by the pooled standard deviation of the observed test-retest reliability. This effect size translates, for example, in an improvement of 5.8 points (on an IQ-like index score) within the treatment group versus an improvement of 1.0 point within the active control group, with both groups showing a variance of 10 points (2/3 of a standard deviation, as observed in other composite cognitive performance data) from pre-assessment to post-assessment. Recently published studies that examined the efficacy of the core exercise (TAPAT) in participants with acquired brain injury (*n* = 40) documented effect sizes of 0.75 [32] and 0.69 [33] on the composite attention measure; we believe this is a reasonable estimate of the plausible effect size in this trial. Also, a recent meta-analysis of the effect size of cognitive rehabilitation documented an average between groups effect size of 0.31 [58] in the population of studies used to support the practice guidelines for cognitive rehabilitation [59, 60]. Based on this analysis, we will enroll 120 participants into the trial. We intend to enroll equally from each site (60 per site).

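### The secondary aim of demonstrating equivalent safety is not supported by the design as stated: the trial is sized on efficacy alone, lists no safety outcome, and gives only a difference-type p < 0.05 criterion

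*Protocol article*

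**What the plan says.** - **Aim.** Aims and hypotheses sets out, as a secondary aim, to "demonstrate equivalency in safety reported between the treatment and control groups", and attributes it to an FDA requirement.
- **Size.** Strengths states that "we will enroll 120 participants into the trial", derived from an "effect size of 0.50 on an outcome measure". Randomization says the "allocation ratio is 1:1", and Overall design and timeline puts sixty in each arm.
- **Outcomes and decision rule.** The outcome lists, both in Primary and secondary outcome measures and in Data analysis, hold cognitive, functional, sleep, quality-of-life and mindfulness measures. None is a safety variable. After the list of secondary outcomes comes the only criterion: "The criterion for statistical significance is *p* < 0.05". The quantity singled out for significance is the group-by-time interaction in the mixed model.
- **Safety data.** In Foreseeable risks, Risk Management & Emergency Response, participants are encouraged to report any adverse effect, weekly check-ins give them the chance to do so, and depression and suicidality are assessed at baseline, week 13 and week 26. Unanticipated adverse device effects (UADEs) have a specific route: "All UADEs will be documented on a standardized eCRF", with classification by the blinded site investigator. The same section calls participation minimal risk and says prior studies reported no serious adverse effects.

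**The concern.** An undertaking to demonstrate equivalence is stronger than one to monitor or describe safety. It needs a quantity to compare, a largest difference that would still count as equivalent, and enough information to rule out anything larger. The article ties its sample size and its significance rule to efficacy. If safety were judged by the same kind of rule, a p-value above 0.05 would show only that no difference was detected. With few events per arm, that result is likely whether or not the arms differ.

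At stake is a reassuring safety statement, linked by the article to a regulator, that the data might be unable to support. The primary efficacy conclusion is not affected.

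**Working it through.** **Inputs.** From the article: 60 per arm, 1:1 allocation, p < 0.05 (taken as two-sided, since sidedness is not stated), d = 0.50. The article gives no adverse-event rate and no margin, so those below are assumptions shown as ranges. Loss to follow-up is ignored, which favours the trial.

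**1. The plan's own figure.** For a two-sided 0.05 test with 80% power, n per arm = 2(1.960 + 0.842)² / 0.50² = 62.8, so 63 per arm or 126 in total. At 60 per arm the power is Φ(0.50·√30 − 1.960) = 78.2%. The article states no power, so 120 can be neither confirmed nor refuted. What matters here is that no event rate or safety margin enters the calculation.

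**2. What 60 per arm says about a difference in rates.** Newcombe's interval combines the two Wilson intervals. For equal counts it is ±√[(p − l)² + (u − p)²], where l and u are the Wilson limits for one arm.

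| Events per arm | Wilson 95% limits, one arm | 95% CI for the difference |
|---|---|---|
| 0/60 | 0 to 6.0% | ±6.0 points |
| 3/60 (5%) | 1.7% to 13.7% | ±9.3 points |
| 6/60 (10%) | 4.7% to 20.1% | ±11.5 points |

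**3. What a difference test would do.** Fisher's exact test at 60 per arm gives p = 0.057 for 5 events against 0 and p = 0.027 for 6 against 0, so six against none is the first significant split from zero. Summing the two binomial distributions over all tables with p ≥ 0.05 gives:

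| True rates | Probability of non-significance |
|---|---|
| 5% vs 1% | 95% |
| 10% vs 5% | 91% |
| 15% vs 5% | 67% |
| 20% vs 10% | 75% |

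Even a tripling from 5% to 15% would be missed about two times in three.

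**4. What an equivalence test could do.** Two one-sided tests at 0.05 amount to requiring the 90% interval to lie within ±margin. Power at a true difference of zero, by full enumeration with the Newcombe 90% interval:

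| Event rate in both arms | ±5 points | ±10 points | ±15 points |
|---|---|---|---|
| 1% | 30% | 96% | more than 99% |
| 2% | 9% | 83% | 99% |
| 5% | 0.2% | 45% | 91% |
| 10% | about 0% | 13% | 68% |

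The ±5 column can be checked by hand. The 90% interval is ±4.3 points for 0/60 against 0/60 but already ±5.6 for 1/60 against 1/60, and 1 against 0 reaches 7.1. Only a trial with no events at all passes, so power is (1 − rate)^120: 0.99^120 = 30%, 0.98^120 = 9%, 0.95^120 = 0.2%.

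**5. What the attainable margin would allow.** At a 1% rate, +10 points means 11%, an eleven-fold increase. At 2% it means 12%, six-fold. Passing such a margin with rare events gives limited reassurance.

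**The case against.** The strongest reply is that this is a journal article. A safety endpoint, margin and test may well stand in the full protocol or the analysis plan, neither of which is shown, and an article commonly leaves them there. That is right, and the absence of a margin is not the point. The sample size and outcome lists that the article does fix are the point: a margin set elsewhere would not change 60 per arm or the widths in step 2.

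Three stronger readings are tempting, and the article does not support them:

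- **That equivalence cannot be shown with 60 per arm.** This is false as an absolute. If events are as rare as the minimal-risk description suggests, a ±10-point margin has 83% to 96% power at rates of 2% and 1%, and no events in either arm would satisfy even ±5 points.
- **That only serious, unanticipated events are captured.** The article elicits any adverse effect, holds weekly check-ins, schedules depression and suicidality assessments, and in Data management sends all study-related data to the eCRF. UADEs are merely the only adverse events given a specific documentation and classification route.
- **That sparse counts will be announced as equivalence.** No passage applies p < 0.05 to safety or says how a null safety result will be read. This is a risk that a reader may infer, not a stated plan.

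It is also fair to say that this is one clause among the secondary aims and drives neither the sample size nor the primary conclusion.

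**Conclusion.** The concern holds in limited form. The article promises to demonstrate safety equivalence, but the design it describes does not support that promise: sizing is for efficacy only, no safety variable is listed as an outcome, and the one criterion given is for a difference. A non-significant safety comparison would not show equivalence. With no events at all the data would still be compatible with a difference of about 6 points either way at 95% confidence. A formal claim would be within reach only with a margin of around 10 points or wider and event rates of a few per cent or less.

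The power figures rest on assumed margins and rates, equal true rates in both arms and full follow-up of 60 per arm. Dropout would widen the intervals. The conclusion that a non-significant difference is not evidence of equivalence rests on none of these assumptions.

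**What to change.** Restate the aim as describing and comparing adverse-event rates between arms, with 95% confidence intervals for the difference and no claim of equivalence. Tabulate by arm all adverse effects already elicited, including those voiced at weekly check-ins and the results of the depression and suicidality assessments, and not UADEs alone.

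If the equivalence claim must stay, fix the safety endpoint and the margin before any comparison by arm, test with two one-sided tests, and state the power at 60 per arm over a plausible range of event rates.

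The cost is a less favourable safety claim and a little extra tabulation. No additional participants or visits are needed.
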